## Results

### Trial Status

Participant recruitment and data collection ran from June 2020 to June 2021. This study was fully conducted during the COVID-19 pandemic. Figure 6 shows the recruitment of the study participants together with daily new COVID-19 cases as a percentage of the population in Iceland (data from the study by Ritchie et al [46]).

**Figure 6 figure6:**
[figure not shown]
Study progress in Iceland during the worldwide COVID-19 pandemic.

### Trial Participants

The approximate average duration of all assessments at each study visit was as follows: visit 1, 1.48 (SD 0.25; range 1.10-2.17) hours; visit 2, 2.70 (SD 0.40; range 0.88-3.38) hours; visit 3, 2.17 (SD 0.33; range 1.47-2.90) hours; and visit 4, 1.63 (SD 0.28; range 0.83-2.18) hours. Table 1 shows demographic and conventional end point data. Medical history and comorbidities are listed in Multimedia Appendix 3.

**Table 1 table1:** Demographics and baseline characteristics of the study population (N=50).

Demographics		Cohort 1: controls (n=13)	Cohort 2: presymptomatic (n=12)	Cohort 3: predementia (n=13)	Cohort 4: mild dementia (n=12)
**Age (years)**					
	Values, mean (SD)	68.1 (3.7)	72.4 (4.3)	70.6 (4.1)	69.3 (6.5)
	Values, median (range)	68 (63-73)	71 (65-78)	71 (62-78)	68 (61-80)
**Sex, n (%)**					
	Male	9 (69)	7 (58)	9 (69)	8 (67)
	Female	4 (31)	5 (42)	4 (31)	4 (33)
**Education, n (%)**					
	Higher education	9 (69)	4 (33)	4 (31)	3 (25)
	Upper secondary education	4 (31)	6 (50)	5 (39)	6 (50)
	Compulsory education	0 (0)	2 (17)	4 (31)	3 (25)
**BMI (kg/m^2^)**					
	Values, mean (SD)	26.7 (2.7)	25.3 (3.9)	26.6 (4.3)	26.7 (3.4)
	Values, median (range)	27.2 (22.5-31.4)	24.4 (20.5-34.1)	25 (21.1-33.5)	25.9 (23-35.4)
**MMSE^a^**					
	Values, mean (SD)	29.5 (1.1)	29.7 (0.7)	27.4 (2.2)	21.8 (1.5)
	Values, median (range)	30 (26-30)	30 (28-30)	28 (24-30)	22 (20-25)
**RBANS^b^**					
	Values, mean (SD)	101 (7)	98.4 (8.8)	75.7 (12.2)	66.3 (8.8)
	Values, median (range)	101 (88-115)	97 (84-118)	74 (49-95)	65 (55-83)
**CDR^c^ global**					
	Values, mean (SD)	0.04 (0.1)	0 (0)	0.5 (0)	0.7 (0.2)
	Values, median (range)	0 (0-0.5)	0 (0)	0.5 (0.5-0.5)	0.5 (0.5-1)
**CDR-SOB^d^**					
	Values, mean (SD)	0.1 (0.2)	0 (0)	1.7 (0.9)	3.5 (1.1)
	Values, median (range)	0 (0-0.5)	0 (0)	1.5 (0.5-3)	3.5 (1.5-5)
**ECog^e^ patient**					
	n-Nan^f^	1	0	1	0
	Values, mean (SD)	44.4 (4.7)	44.5 (4.5)	68.3 (28.5)	64.4 (10.2)
	Values, median (range)	44 (39-57)	44.5 (39-54)	56.5 (46-140)	67.5 (49-80)
**ECog caregiver**					
	Values, mean (SD)	45.5 (6.2)	47.5 (9.3)	67.6 (12.3)	88.7 (28.8)
	Values, median (range)	42 (39-56)	43 (39-65)	70 (53-91)	83 (53-137)
**NPI-Q^g^**					
	Values, mean (SD)	0.23 (0.6)	1.1 (2.2)	5.6 (5.3)	5.3 (6.9)
	Values, median (range)	0 (0-2)	0 (0-7)	4 (0-13)	3 (0-22)
**FACIT^h^**					
	n-Nan	0	0	1	1
	Values, mean (SD)	10 (2.3)	9.3 (3.7)	14.4 (7.8)	13.2 (5.4)
	Values, median (range)	11 (6.5-13)	8.75 (6-20)	11.2 (7-33)	11 (5.5-22)

^a^MMSE: Mini-Mental State Examination.

^b^RBANS: Repeatable Battery for the Assessment of Neuropsychological Status.

^c^CDR: Clinical Dementia Rating scale.

^d^CDR-SOB: CDR Sum of Boxes.

^e^ECog: Everyday Cognition.

^f^This is the number of missing values (eg, 1 study participant with a missing result for Everyday Cognition in cohort 1).

^g^NPI-Q: Neuropsychiatric Inventory–Questionnaire.

^h^FACIT: Functional Assessment of Chronic Illness Therapy.

## Discussion

### Expected Findings

The expected main findings of this study are as follows: (1) the accuracy of each of the 10 technologies in classifying participants into 4 cohorts according to the severity of cognitive impairment and dementia; (2) the psychometric properties of each of the digital technologies tested, including acceptable range (ceiling and floor effects), concurrent validity (correlation of ≥1 outcome measure of each of the technologies to traditional paper-and-pencil tests in AD), reliability (concordance of test and retest), and responsiveness (the sensitivity to change in a mild cognitive challenge model); and (3) feasibility of applying these technologies in drug trials based on study participant feedback.

Digital technologies hold promise in amending psychometric limitations associated with many conventional paper-and-pencil end points and transforming the way drug treatment effects are measured in clinical trials. For example, the digital pen used in this study to augment standard cognitive tests may reduce subjectivity and variability of well-established paper-and-pencil tests such as the clock-drawing test, trail-making test, or digit-symbol substitution test [42]; computerized testing implemented on tablets or smartphones with short cognitive test batteries may allow more frequent monitoring of cognition in the real world, thereby reducing variability and bias [47-49]; eye tracking while reading and voice analytics of conventional picture description tests may provide direct physiological assessments of cognition, which may increase sensitivity [30-37]; and AR or virtual reality testing may introduce more real-life assessments in a clinical setting [50,51]. More accurate and reliable efficacy end points could potentially reduce the number of failed or inconclusive trials and allow for more efficient drug development through shorter, smaller, less costly, and less burdensome drug trials, ultimately allowing more drugs to be studied and medicines to reach patients faster. However, it remains unclear how to best evaluate a wide range of novel and promising technologies, how to use them to derive efficacy end points, and how to advance them through early drug development processes.

The MEDIA study is an effort to establish a method for efficiently evaluating a range of technologies in a single study. Within the drug development framework, it is important to collect validation data and better understand operational feasibility before attempting to implement novel digital technologies in clinical drug trials. Clinical trials of drug interventions are highly complex and effortful undertakings and typically do not offer a good opportunity to study multiple novel digital end points. Often, these trials are already quite onerous for both participants and clinical sites, and the introduction of additional end points risks overburdening and jeopardizing the integrity of the primary objective of the study. Hence, carefully designed methodology studies such as the MEDIA study derisk drug intervention trials and offer valuable insights into the ceiling and floor effects, concurrent validity, reliability, and responsiveness of novel end points, as well as information about implementation, patient acceptance, and any operational complexity that a novel end point might add to a drug intervention trial.

A previous noninterventional study of 8 digital technologies for characterizing unipolar depression [52] successfully identified promising digital end points to advance as exploratory end points in numerous early phase clinical drug trials. However, this study lacked a challenge model and hence did not provide insights into sensitivity to change. A benign cognitive challenge model was implemented in the current MEDIA study, and the results will demonstrate if this is a feasible approach to study sensitivity to change in future methodological studies. The digital technologies included in the MEDIA study are in various stages of development. Some are already well established, with considerable validation data and clinical trial experience, whereas other technologies are still in early development. This will be taken into account when evaluating their performance.

Health authorities have published guidelines on the data required for a novel end point to be considered validated or qualified from a regulatory perspective [53-56]. Among the important qualities that an end point needs to meet are good psychometric properties (eg, lack of ceiling and floor effects), assay sensitivity (ie, sensitivity to drug treatment effects or disease progression), sufficient reliability and validity (eg, test-retest reliability and concurrent validity), and clinical meaningfulness. There are many ways of establishing clinical meaningfulness. This study used a participant feedback survey to understand patient acceptance of the end points and whether they considered the assessments meaningful to the problems they faced in their daily lives. Moreover, the outcomes of the novel digital end points will be correlated with the outcomes of conventional paper-and-pencil assessments of function, offering another method for assessing clinical meaningfulness. The topic of regulatory qualification of novel clinical end points is beyond the scope of this paper and will be addressed in a future publication.

Good concurrent validity occurs when a new end point demonstrates an appropriate correlation with an established gold standard. This is an important psychometric feature of sound clinical trial end points. However, as conventional neuroscience end points often display poor psychometric properties in various stages of AD (eg, ceiling effects in early predementia stages and floor effects in overt dementia), as well as rater errors and cultural bias, one might start to question the appropriateness of some of these conventional end points in establishing the concurrent validity of novel end points. Moreover, conventional end points are rarely pure measures of a single cognitive domain. For example, performing a memory task comprising a word list learning task relies not only on intact memory processes but also on attention, language comprehension, working memory, and executive function. Hence, it may be difficult to accurately interpret any potential lack of correlation between the conventional and novel cognitive end points. This dilemma will likely continue to challenge the development and validation of novel digital end points.

This study was conducted during the COVID-19 pandemic (SARS-CoV-2 virus pandemic). The full impact of the pandemic on this study is not clear [57]. First, the study was delayed at the beginning because of the implementation of preventive measures, and the overall duration of the project was prolonged because of various measures such as phases of lockdowns and quarantine. Originally, the planned duration of the study was approximately 6 months; however, this was prolonged to 1 year. Second, social distancing and infection control measures may have affected the digital assessments. For example, the use of face masks may have affected the quality of voice recordings and gait assessments. Finally, restrictions on social gatherings and regarding lockdown of commercial activities may have contributed to feelings of lethargy, anxiety, social isolation, disorientation to time, and a feeling of *every day is the same*. The psychological impact of the pandemic is yet to be further elucidated; however, it is clear that responses to questions about activities of daily living and neuropsychiatric symptoms during such unprecedented times are likely to be affected [58].

### Limitations

This exploratory methodology study has several limitations. Most notably, the small sample size necessitates findings to be confirmed in larger trials. Second, as this is a noninterventional study, it is difficult to establish sensitivity to change. One of the greatest risks that conventional end points pose to clinical drug development in neuroscience is the lack of sensitivity to changes and the possibility of missing important drug treatment effects. Hence, it is of utmost importance to demonstrate good assay sensitivity when studying novel digital end points to be implemented as efficacy measures in clinical trials. In this study, a benign cognitive challenge model was used in an attempt to assess the sensitivity to change of each digital end point. However, it is difficult to determine what challenge will be sufficient to reliably produce cognitive impairment in a cross-sectional study such as this one. Moreover, producing fatigue through late-night testing may not affect all cognitive domains to the same extent. Hence, the challenge model may affect participant performance on the various digital end points differently. In addition, as participants had no expectations of treatment benefits in this noninterventional study, it is possible that the digital end points would show different sensitivities to change in a clinical drug trial. Sensitivity to drug treatment effects cannot be fully evaluated until the digital end point is studied in a drug intervention trial. This is often the key validation data that novel digital end points are missing and is the most challenging data to acquire. This was a single-site study that provided limited information on how scalable the digital technologies are to multisite global trials and to what extent culture and language may be confounding factors. Finally, although the study included more men (33/50, 66%) than women (17/50, 34%), the proportions of men and women were, overall, similar across the 4 cohorts. It should also be noted that the education level was not evenly distributed across the cohorts; there was a greater number (and percentage) of participants with higher education in cohort 1 (9/13, 69%) than in cohort 2 (4/12, 33%), cohort 3 (4/13, 31%), and cohort 4 (3/12, 25%). As the education level may potentially be an important confounder, statistical analysis will be adjusted for it, as appropriate. Owing to the invasive procedures and sensitive biomarker information, there were no prospective CSF samples or PET imaging conducted in this noninterventional methodology study. Amyloid status was based on historical investigations that had to be aged <2 years. Historical reports were based on both CSF analysis (48/50, 96%) and PET imaging (2/50, 4%), and this study was not able to confirm any potential changes that may have occurred in amyloid status. Moreover, this study could not confirm any potential discrepancies between the 2 amyloid assessment procedures.

The findings of this study are planned to be disseminated in peer-reviewed journals and at key scientific conferences in 2022 and 2023.

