### Conventional Paper-and-Pencil End Points

#### The Repeatable Battery for the Assessment of Neuropsychological Status

The Repeatable Battery for the Assessment of Neuropsychological Status (RBANS) [15] is a clinical tool specifically designed for both diagnostic purposes and for tracking changes in neurocognitive status over time. The RBANS was selected for the MEDIA study as this battery was designed to detect and characterize the earliest neurocognitive changes associated with dementia. RBANS scores have been reported to be correlated with cerebral amyloid in both cognitively normal individuals [16] and patients with MCI because of AD [17]. The RBANS takes 30 to 40 minutes to administer and generates age-adjusted index scores for 5 neurocognitive domains that are used to calculate a total scale index score (total possible range 40-160; a higher score indicates better cognitive function). It comprises the following domains with associated subtests used for index scores: (1) Immediate Memory (List Learning and Story Memory), (2) Visuospatial and Constructional (Figure Copy and Line Orientation), (3) Language (Picture Naming and Semantic Fluency), (4) Attention (Digit Span and Coding), and (5) Delayed Memory (List Recall, List Recognition, Story Memory, and Figure Recall).

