### Statistical Analysis

As this is an exploratory study, the sample size was chosen pragmatically to balance statistical and feasibility considerations. Data from 12 participants per cohort were considered to provide sufficient information for the study objectives [45].

Descriptive statistics (ie, mean, median, range, and SD) of the total score from each conventional end point and questionnaire will be reported by the cohort. Estimates of the between-cohort standardized differences in the corresponding total scores will be provided.

Digital technologies will produce ≥1 outcome variable (features) for each participant and assessment time. On the basis of these features, psychometric properties will be assessed: acceptable range (ceiling and floor effects), reliability (test-retest variability), validity (correlation to conventional end points), and responsiveness (change from test and retest to challenge) as appropriate. Various statistical rules for classifying participants into cohorts will be explored. The goodness of these rules will be assessed by calculating the sensitivity, specificity, positive predictive value, and negative predictive value. Receiver operating characteristics curves will be constructed to determine cutoff points with the best trade-off between sensitivity and specificity. Data from the participant feedback survey will be summarized descriptively.

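### Education is the only covariate named for adjustment, but between controls and amyloid-positive healthy participants age is the larger imbalance (about 1.08 SD) and could pass for a presymptomatic signal

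*Protocol article*

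**What the plan says.** The Limitations section reviews balance across cohorts with Table 1 in hand. On sex it concludes that "the proportions of men and women were, overall, similar across the 4 cohorts". It calls education unevenly distributed, gives the cohort percentages, and draws the consequence: "As the education level may potentially be an important confounder, statistical analysis will be adjusted for it, as appropriate". The age row of Table 1 is not discussed there, and age is named nowhere in the article as an imbalance, a limitation or a covariate.

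The Statistical Analysis section names no covariate. On classification it says "Various statistical rules for classifying participants into cohorts will be explored", and then "Receiver operating characteristics curves will be constructed to determine cutoff points with the best trade-off between sensitivity and specificity".

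Among the conventional end points, the RBANS "generates age-adjusted index scores for 5 neurocognitive domains". Most digital outputs are described as raw quantities: latency and errors, gait parameters, counting rate, speech variables, eye movements, time to finish a drawing. The DCTclock section is an exception, since its results are compared with normative data. It does not say whether those norms take account of age.

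**The concern.** Cohorts 1 and 2 are both cognitively healthy, and conventional tests barely tell them apart (MMSE 29.5 versus 29.7; RBANS 101 versus 98.4). This is where the article hopes digital measures will add something, because its Abstract and Conclusions speak of detection at earlier stages.

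The amyloid-positive cohort is the older one. Slowing or error that comes with age alone would point in the same direction as early impairment. With education as the only named adjustment, a feature that tracks age could seem to classify presymptomatic disease. The Introduction says that technologies meeting success criteria move on to phase 2 as exploratory end points, so a false lead would carry forward.

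**Working it through.** **Inputs (Table 1).** Age: cohort 1, 68.1 (SD 3.7), n = 13; cohort 2, 72.4 (4.3), n = 12; cohort 3, 70.6 (4.1), n = 13; cohort 4, 69.3 (6.5), n = 12. Education (higher / upper secondary / compulsory): cohort 1, 9/4/0; cohort 2, 4/6/2. RBANS: 101 (7) and 98.4 (8.8). The article gives no correlation between any digital feature and age, so r = 0.2 to 0.7 is assumed.

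**The article's own figures.** The shares with higher education reproduce: 9/13 = 69%, 4/12 = 33%, 4/13 = 31%, 3/12 = 25%. No age difference is computed in the article.

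**Age, cohort 1 versus 2.**
- Pooled SD = √[(12 × 3.7² + 11 × 4.3²)/23] = √(367.67/23) = 4.00.
- d = (72.4 − 68.1)/4.00 = 1.08; 95% CI 0.22 to 1.91 (noncentral t).
- t = 1.075/√(1/13 + 1/12) = 2.69 on 23 df, p = 0.013.
- AUC of age alone, assuming normality: Φ[4.3/√(3.7² + 4.3²)] = Φ(0.758) = 0.78.

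**Education, same pair.**
- Three levels: of 13 × 12 = 156 pairs, the cohort 2 member has less education in 9 × 8 + 4 × 2 = 80, and 9 × 4 + 4 × 6 = 60 are ties. AUC = (80 + 30)/156 = 0.71.
- Higher education versus not: standardised difference 0.77, AUC 0.68.

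**RBANS, same pair.** The pooled SD is 7.91, so d = 2.6/7.91 = 0.33. AUC = Φ[2.6/√(7² + 8.8²)] = Φ(0.231) = 0.59.

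**A feature with no amyloid effect.** If it correlates r with age within cohort, its apparent d is r × 1.075 and its AUC is Φ(r × 1.075/√2):

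| r (assumed) | apparent d | AUC |
|---|---|---|
| 0.2 | 0.22 | 0.56 |
| 0.3 | 0.32 | 0.59 |
| 0.5 | 0.54 | 0.65 |
| 0.7 | 0.75 | 0.70 |

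It equals the RBANS at r = 0.3 and exceeds it above that.

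**False-positive rate.** In 4,000 simulated data sets per r, with ages scaled to the Table 1 means and SDs, a 5% t test without age flags such a feature in 10.9% (r = 0.3) or 20.6% (r = 0.5). With age as a covariate the rates are 5.5% and 5.1%.

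**Other pairs.** Age d, as later minus earlier cohort: 1 vs 3, 0.64; 1 vs 4, 0.23; 2 vs 3, −0.43; 2 vs 4, −0.56; 3 vs 4, −0.24. Mean age does not rise with severity. In the three negative pairs the less impaired cohort is the older one, so age would tend to blur the separation there.

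**Price of adjustment, cohort 1 versus 2.** Cohort explains R² = t²/(t² + 23) = 0.24 of the age variance. The standard error of the cohort contrast grows by √[1/(1 − 0.24)] = 1.15, before any gain from the residual variance that age removes.

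**The case against.** The quoted sentence is a remark in a Limitations section, qualified by what is appropriate, and it does not say that education is the only covariate. Covariate lists commonly sit in an analysis plan, and none is shown here. That stands, so the mere absence of a covariate list is not the point. The point is that the article picks its confounder from observed imbalance and passes over a larger one for this pair.

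Education was also a reasonable choice for a four-cohort study, because it separates cohort 1 from all three others. The four-cohort ANOVA on age gives p = 0.15, and p = 0.013 belongs to the most extreme of six pairs. The size of the gap depends on the denominator: 1.08 with the two-cohort pooled SD, 1.00 with cohort 2's SD, 0.91 with the four-cohort SD of 4.74. All of this is correct, and it confines the point to a pair or two. It does not remove it, because confounding depends on the imbalance in the sample, whatever its p-value.

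A reader might infer that an age-driven feature will be reported as beating the RBANS. The documents do not support that. The correlation is assumed, the feature only ties at r = 0.3, and with 13 and 12 participants the standard error of an AUC near 0.6 is about 0.11 to 0.12 (Hanley-McNeil), so 0.65 and 0.59 cannot be told apart.

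A reader might also infer that digital measures as a group keep the benefit of age while conventional ones lose it. The article supports this asymmetry for the RBANS only. The MMSE, CDR, NPI-Q and ECog are not described as age-adjusted, and DCTclock uses norms.

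**Conclusion.** The point holds for cohort 1 versus cohort 2 and, more weakly, for cohort 1 versus cohort 3. Followed as written, the article's only stated adjustment leaves the comparison of amyloid-negative with amyloid-positive healthy participants open to confounding by age. That age is the larger imbalance for this pair follows from Table 1, with normality assumed for the AUC of age. The size of any spurious digital signal rests on the assumed correlation with age and on a feature with no amyloid effect.

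It would go too far to say that age confounds the four-cohort classification as a whole. It would also go too far to say that the sponsor will not adjust for age, since the analysis plan may do so.

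Severity: should-fix. The study is exploratory, the article says its findings need confirmation in larger trials, and reliability, responsiveness, range, feasibility and acceptance do not depend on this contrast.

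**What to change.** - Name age, as a continuous covariate, beside education for between-cohort comparisons and classification rules, at least for cohorts 1 versus 2 and 1 versus 3.
- Report the AUC of age plus education alone as the benchmark for each digital technology and for each comparator that is not already age-adjusted. It needs participant-level data, because Table 1 does not give the joint distribution.
- For the RBANS, avoid adjusting for age a second time, or flag it where it is done. State whether the DCTclock norms take account of age.
- Add the age imbalance to the limitations.

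The cost is a short paragraph, since age is already recorded. In the analysis, the standard error of the cohort 1 versus 2 contrast rises by a factor of about 1.15 at most, apart from the lost degree of freedom. Adjusted estimates with about 12 participants per cohort will be imprecise and should be shown with intervals. A cross-validated gain in AUC for every contrast would be too noisy at about 25 people per pair to be worth requiring.
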